## Abstract

**Background**. Postpartum haemorrhage (PPH) is a leading cause of maternal death. Tranexamic acid (TXA) has the potential to reduce bleeding and a large randomized placebo controlled trial of its effect in women with PPH (The WOMAN trial) is underway. TXA might also affect coagulation factors and platelets. 
**Objectives**. To examine the effect of TXA on thrombin generation, platelet function, fibrinogen, D-dimer and coagulation factors in women with PPH. 
**Methods**. We will conduct a sub-study within the WOMAN trial. Women with clinically diagnosed primary PPH after vaginal or caesarean delivery are eligible for inclusion. Blood samples will be collected at baseline and 30 minutes after the first dose of study treatment. Using platelet poor plasma we will measure thrombin generation, fibrinogen, D-dimer, factor V and VIII, and Von Willebrand factor. Platelet function will be evaluated in whole blood using Multiplate® tests.
**Outcomes**. The primary outcome is the effect of TXA on thrombin generation. Secondary outcomes include the effect of TXA on platelet function, fibrinogen, D-dimer and coagulation factors.

## Abbreviations

ADPtest: Test of Adenosine Di Phosphate; AUC: Area Under Curve; CI: Confidence Interval; CBC: Complete Blood Count; DMC: Data Monitoring Committee; ETP: Endogenous Thrombin Potential; FV: Coagulation Factor V; FVIII: Coagulation Factor VIII; ICH GCP: International Conference on Harmonisation of Good Clinical Practice; LT: Lag Time; LSHTM: London School of Hygeine and Tropical Medicine; PH: Peak Height; MPV: Mean Platelet Volume; PPH: postpartum haemorrhage; SAP: Statistical Analysis Plan; SOP: Standard Operating Procedure; TtP: time to peak; TGA: Thrombin Generation Assay; TXA: Tranexamic Acid; TRAPtest: Test of Thrombin Receptor of Thrombocyte; TCC: Trial Coordinating Centre; TSC: Trial Steering Committee; vWF: Coagulation Factor Von Willebrand.

## Background

Tranexamic acid (TXA) reduces bleeding by inhibiting the enzymatic degradation of fibrin blood clots by the serine protease plasmin. During fibrinolysis, plasminogen binds to fibrin via lysing binding sites, where it is converted to the active fibrinolytic enzyme plasmin by tissue plasminogen activator. TXA is a molecular analogue of lysine that inhibits fibrinolysis by reducing the binding of plasminogen to fibrin. TXA reduces surgical bleeding and in 2010, the CRASH-2 trial showed that TXA reduces death due to bleeding in trauma patients (
Roberts & Prieto-Merino, 2014). TXA also has the potential to reduce death due to bleeding in PPH. The WOMAN trial is investigating the effect of TXA on mortality and morbidity in women with PPH.

In addition to its role in fibrinolysis, plasmin has various effects on coagulation factors. Coagulation factors V (FV) and VIII (FVIII) are first activated and then inactivated by plasmin. The initial activation of these factors may generate enough thrombin to have a pro-coagulant effect. Plasmin might also promote thrombin generation by inactivating tissue factor pathway inhibitor, a major inhibitor of tissue factor-mediated thrombin generation (
Godier *et al.*, 2012).
Ogiwara *et al.* (2010) showed that thrombin generation is increased in the presence of plasmin. If plasmin increases thrombin production, TXA, by inhibiting plasmin production, should reduce thrombin generation.

Although TXA reduces bleeding by inhibiting fibrinolysis, it may reduce bleeding through other mechanisms. For example, TXA may improve platelet function (
Boylan *et al.*, 1996). The exposure of platelets with plasmin induces platelet activation (
Ervin & Peerschke, 2001). Plasmin activates platelets via different mechanisms, such as stimulating the arachidonic acid cascade, and inducing platelet degranulation and complement activation (
Godier *et al*., 2012). The main effect of TXA on platelet function may be due to the inhibition of plasmin, and consequently the decrease of plasmin’s multifactorial induction on platelets.

TXA improved platelet function in cardiac surgery patients, with impaired platelet function caused by preoperative exposure of antiplatelet therapy, such as clopidogrel (
Shi *et al.*, 2013). Another study in cardiac surgery patients (
Weber *et al*., 2011) noticed that administration of TXA significantly improved platelet function by attenuating platelet aggregation defects created by antiplatelet treatment.

In patients with chronic renal failure, administration of TXA corrected platelet aggregation defects (
Mezzano *et al*., 1999), and as result improved platelet function. Also,
Sabovic *et al.* (2005) reported that platelet dysfunction in haemodialysis patients was effectively corrected with long term administration of TXA at a low dose.

## Methods and study design

### Objective

The study will assess the effect of TXA on thrombin generation, coagulation factors and platelet function in women with PPH, in particular, the effects of TXA on thrombin generation, factor V (FV), factor VIII (FVIII), Von Willebrand factor (vWF), fibrinogen, D-dimers and platelet function. We hypothesize that by inhibiting plasmin, TXA will decrease thrombin generation, and modify platelet activity, FV, FVIII and vWF levels, in patients with PPH.

### Trial design

The WOMAN-ETAPlaT is a sub-study of the World Maternal Antifibrinolytic Trial, an international randomized, double blinded, placebo-controlled trial. As a sub-study, there are no changes to the study design of the WOMAN trial, but for the specific design of the sub-study there are some additional examinations and laboratory tests.

***Participants and eligibility criteria.***
*Inclusion criteria*: Participants in the study are women ≥18 years old with a clinical diagnosis of postpartum haemorrhage (PPH) after vaginal or caesarean birth. All available treatment for PPH should be given, and inclusion in the study should be considered as soon as possible after patient consent has been obtained. Clinically diagnosed PPH can be established with one of the following conditions: amount of blood lost following vaginal birth is >500mL or >1,000mL after caesarean birth; or enough blood loss has compromised the patient’s hemodynamic status.
*Exclusion criteria*: Patients diagnosed with PPH, for whom the physician believes that there is a secure indication or contraindication for use of TXA, should not be randomised.

***Study setting.*** For the conduct of this sub-study, a single site has been chosen, the Obstetric Gynaecology University Hospital ”Koço Gliozheni” in Tirana, Albania. This is justified because PPH is the main cause of maternal mortality in Albania. The hospital offers tertiary health care and is a national referral hospital for other obstetric gynaecology hospitals in the country.

***Interventions.*** Patients with clinically diagnosed PPH and fulfilling the eligibility of the WOMAN trial will be randomized into the study after the administration of the standard treatments for PPH. As soon as primary PPH is diagnosed, the study drug (TXA or placebo) will be administered as soon as possible alongside all other clinically indicated treatments for PPH. Each trial treatment pack contains two doses, and each dose contains two ampoules of 500mg TXA or placebo (sodium chloride 0.9%).

### Outcomes

***Measures of the primary and secondary outcomes of ETAPlaT study.*** The primary outcome will be the effect of TXA on thrombin generation [thrombin generation assay (TGA) parameter – endogenous thrombin potential (ETP)]. Secondary outcomes will include the effect of TXA on platelet function (Multiplate® tests: ADPtest and TRAPtest), fibrinogen, D-dimer and FV, FVIII, vWF levels, and other TGA parameters [lag time (LT); time to peak (TtP); and peak height (Ph)]. Levels of all parameters will be assessed on two venous blood samples, collected at the baseline and between 30±15 minutes after the first dose of study treatment is given.

Further secondary outcomes will include assessment of the relationship between these parameters, patient demographics and clinical data (in the time frame from randomization to the patient discharge from the hospital or until 42 days).

***Outcomes of the main study WOMAN trial.*** The WOMAN trial will not provide information about platelet function, thrombin generation, fibrinogen, D-dimers and coagulation factors V, VIII and vWF in patients receiving TXA/placebo. However, the most reliable estimates of the effects of TXA on the outcomes for women with PPH will be provided by the WOMAN trial.

### Sample size

We aim to assess if TXA, when compared to a placebo, has an effect on change over time on the TGA parameter, ETP. Therefore, the sample size calculation is based on this parameter. Patients are expected to be equally allocated between the two intervention groups; 88 patients per group (total, 176 patients) are needed to detect the difference of ETP 243nM/min, with a change between the groups at a 5% significance level with a power of 80%.

### Randomization and blinding

Patients with a clinical diagnosis of PPH, who are eligible for the WOMAN trial, after having completed the informed consent procedures, will be randomly assigned to receive either TXA or placebo. Patients randomised in the trial will receive the study drug (TXA/placebo) by intravenous injection. The lowest available number of the pack will be used first and then subsequently other packs from the box that contains 8 study treatment packs. The blinding process will be carried out by an independent supplier, who will mark the study drug with the blinded label. The vials and packages will be the same, and the randomisation number will be used as the pack identification.

### Procedures before/after the study treatment administration, blood sample collection and analysis

Immediately after patient is randomized, two test tubes (3mL and 5mL) of venous blood will be taken and the first dose of trial treatment will be administered. About 30±15 minutes after the administration of the first dose of trial drugs, two more test tubes (3mL and 5mL) of venous blood will be collected. If a woman continues to bleed and a second dose of trial treatment is required, the second blood sample will be taken before this is given (
Figure 1).

**Figure 1. f1:**
[figure not shown]
Algorithm of the WOMAN-ETAPlaTsub-study. Black boxes: Standard procedure of the WOMAN trial. Red boxes: Additional procedures required for the ETAPlaT sub-study.

Samples of the 3mL tubes (hirudine) whole blood will be analyzed immediately at the hospital in Tirana, Albania for platelet function using a Multiplate Platelet Function Analyzer (Dynabyte GmbH, Munich, Germany).

Samples of 5mL tubes (sodium citrate 3.2%) will be centrifuged immediately at 3000xg for 20 minutes, and platelet poor plasma samples will be divided ito two aliquots and preserved at -80°C. These will be transferred to dry ice for later analysis at the Institute of Laboratory Medicine, German Heart Centre in Munich, Germany for TGA, fibrinogen, D-dimers, and FV, FVIII and vWF levels. The temperature storage conditions of the plasma samples will be monitored and recorded daily.

As part of the routine protocol of the hospital, a blood sample for complete blood count (CBC) is taken from every woman in labour prior to delivery. In cases of PPH randomized in the study, another CBC is performed after 4 hours and within 12 hours, depending on the severity of PPH. The pre-post randomization difference in CBC parameters, such as haemoglobin or haematocrit drop, will be evaluated.

Standard operating procedures for handling, storage and analysis of the blood samples and the process for transferring the data to the Trial Coordinating Centre (TCC) are developed by each responsible Institution, and are approved by TCC. Copies are available from the Trial Master File.

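### The haemoglobin/haematocrit drop described as a difference across randomisation runs from a pre-delivery blood count to a severity-timed follow-up, so it does not isolate change after randomisation

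*Protocol article*

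**What the plan says.** The CBC is described in the Protocol article under Procedures before/after the study treatment administration, blood sample collection and analysis, in the text after Figure 1. As hospital routine, "a blood sample for complete blood count (CBC) is taken from every woman in labour prior to delivery". For women randomised with PPH, "another CBC is performed after 4 hours and within 12 hours, depending on the severity of PPH". The quantity to be assessed follows: "The pre-post randomization difference in CBC parameters, such as haemoglobin or haematocrit drop, will be evaluated".

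Under Participants and eligibility criteria, PPH is diagnosed when the "amount of blood lost following vaginal birth is >500mL or >1,000mL after caesarean birth", or when the loss has compromised haemodynamic status. Randomisation therefore comes after that bleed.

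Blood is also drawn at entry: "Immediately after patient is randomized, two test tubes (3mL and 5mL) of venous blood will be taken". No CBC on these tubes is described. The 3 mL tube goes to platelet function testing ("Samples of the 3mL tubes (hirudine) whole blood will be analyzed immediately at the hospital in Tirana, Albania for platelet function"), and the 5 mL citrate tube is spun to plasma for the thrombin generation and factor assays.

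The named laboratory outcomes (section Outcomes) come from samples "collected at the baseline and between 30±15 minutes after the first dose of study treatment is given". CBC change is not among the named primary or secondary outcomes.

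**The concern.** The label invites the reader to take the drop as change since randomisation. The only earlier CBC described precedes delivery, so the interval covers delivery, the haemorrhage that made the woman eligible, and the hours after treatment. The study drug can act only on the last part. Unlike the named laboratory outcomes, this measure has neither a value taken at entry nor a narrow follow-up window.

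Two things are at stake. A mean drop reported within each arm could be read as loss after treatment when much of it may have occurred before. The comparison of raw drops between arms also carries avoidable noise, in a study that lists its small size as a limitation.

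A lesser issue is the follow-up time. It varies over 8 hours with severity, the start of the clock is not given, and the article does not say when severity is judged.

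**Working it through.** The article gives no figure for the CBC measure. Its one calculated figure, "88 patients per group (total, 176 patients) are needed to detect the difference of ETP 243nM/min", concerns ETP. It comes without a standard deviation, so it cannot be reproduced independently, and nothing below depends on it.

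**Step 1: order of events in the text.**

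| Event | Relative to randomisation |
|---|---|
| Routine CBC in labour | before, and before delivery |
| Delivery loss and qualifying bleed | before |
| Randomisation, entry tubes (no CBC described), first dose | time zero |
| Follow-up CBC, 4 to 12 h by severity | after |

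So drop = (pre-randomisation part) + (post-randomisation part).

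**Step 2: bias in the arm comparison.** Allocation cannot affect the pre-delivery value or the loss before entry. Their expected values are equal in the two arms and cancel in the difference between mean drops. What remains in expectation is the difference in mean follow-up haemoglobin.

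**Step 3: how much of the loss precedes entry (illustration).** Share = pre / (pre + post). The pre-entry volumes are the eligibility thresholds; the post-entry volumes of 100 to 1,000 mL are assumptions.

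- 500 mL before: 500/600 = 83%, down to 500/1,500 = 33%.
- 1,000 mL before: 1,000/1,100 = 91%, down to 1,000/2,000 = 50%.

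The thresholds are minimum losses for women who qualify by volume. Women who qualify by haemodynamic compromise may have lost less. These are shares of volume, not of haemoglobin. If 1 g/dL is lost per 500 mL (assumed; range 0.5 to 1.5), the qualifying loss alone contributes about 1 g/dL (0.5 to 1.5) after vaginal birth and 2 g/dL (1 to 3) after caesarean birth.

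**Step 4: noise (illustration).** If the two parts of the drop are independent, SD ratio = √(SD_pre² + SD_post²) / SD_post, and the sample size needed for equal power scales with its square. The SDs, in g/dL, are assumptions.

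- SD_pre 0.5, SD_post 1.0: √1.25 / 1.0 = 1.12; n ratio 1.25.
- SD_pre 1.0, SD_post 1.0: √2 / 1.0 = 1.41; n ratio 2.
- SD_pre 1.5, SD_post 0.5: √2.5 / 0.5 = 3.16; n ratio 10.

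The comparator is a drop measured from a CBC at randomisation, which is not described. These ratios show what the pre-delivery baseline costs, not what adjustment would recover. Adjustment for the pre-delivery value, mode of birth and entry blood loss recovers only the part that those covariates explain.

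**Step 5: severity-dependent timing (illustration).** Suppose severe cases are sampled at 4 h and others at 12 h, and the severe share differs between arms. Spurious difference = drift per hour × 8 h × difference in share.

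- 0.05 × 8 × 0.05 = 0.02 g/dL.
- 0.10 × 8 × 0.10 = 0.08 g/dL.
- Assuming instead a total drift of 0.5 to 1 g/dL over the window and a 10-point difference: 0.05 to 0.1 g/dL.
- Equal severe shares: zero.

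The whole term requires treatment to change the severity that sets the time. If severity is judged before dosing, it is a baseline factor, balanced in expectation.

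**The case against.** The strongest reply is that the label is literally true: one count precedes randomisation and one follows it. The analysis compares randomised groups by intention to treat, so earlier loss cancels between arms. Blinding keeps knowledge of allocation from driving sampling time. The measure appears in procedural text only, and a detailed statistical analysis plan, not shown here, is to be finalised before unblinding.

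Most of this stands. A reader might infer that the drop says nothing about the period after randomisation, or that it would produce a false TXA effect. The documents support neither. The drop contains the post-randomisation change, and the earlier loss adds noise rather than expected bias. A reader might also infer that the follow-up time depends on a post-treatment outcome. That needs severity to be judged after dosing, which the article does not state. Blinding alone would not prevent such a bias, because treatment could act through severity itself.

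Transfusion is a further temptation. Red cells given before the follow-up CBC raise haemoglobin, so a heavy bleeder may show a small drop: about 2 g/dL less after two units, if each unit adds 1 g/dL (assumed). But transfusion follows randomisation, a fixed credit per unit is debatable, and its handling belongs in the analysis plan. It is not an error in this article.

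The reply does not remove the mismatch between label and interval, which is in the text itself, or the noise in the raw drop.

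**Conclusion.** The point holds in a limited form. The drop is a change from before delivery to follow-up and does not isolate change after randomisation. Read within an arm, it would overstate loss after treatment, possibly by more than half of the volume under the assumed losses. Compared between arms, it is unbiased in expectation as far as the baseline is concerned, but noisier than a drop measured from entry. The illustrated sample-size penalty of 1.25 to 10 rests entirely on assumed, independent components. Any timing bias is conditional and small: 0.02 to 0.1 g/dL under the assumed inputs, and zero if severity is balanced.

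The practical weight is modest. CBC change is exploratory, and the primary ETP analysis and its sample size are untouched.

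**What to change.** In the statistical analysis plan, before unblinding:

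1. Call the measure change from pre-delivery to follow-up, and state that the drop within an arm is not to be read as loss after treatment.
2. Compare arms on follow-up haemoglobin and haematocrit by ANCOVA, adjusting for the pre-delivery value and mode of birth, plus blood loss at entry if recorded, in place of the raw drop.
3. State when the 4 to 12 hour clock starts and when severity was judged, and report CBC sampling times by arm as a check on the timing.
4. Optionally, add a transfusion-corrected sensitivity analysis if units and their timing relative to the CBC were recorded.

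The cost is some wording and a little extra analysis. Recruitment and follow-up are complete, so a CBC at randomisation cannot be added. The list of ETAPlaT form items under Data collection does not name CBC results, CBC times or red cell units. Their availability in the trial forms or hospital records should be confirmed first.

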### Ethical considerations, recruitment and consent

Ethical approval for WOMAN ETAPlaT protocols was obtained 28.10.2013 (ref. 6518) from the London School of Hygiene and Tropical Medicine (LSHTM) Ethics Committee in London, United Kingdom, and by the National Ethics Committee in Tirana, Albania on 11.07.2013 (ref. 62) and amendment on 01.12.2014 (ref. 81). PPH is an obstetric emergency and it is not possible to predict which women that will have this complication. In this emergency situation it is important to carry out an informed consent procedure, according to regulatory requirements, and adhere to the ICH-GCP and Declaration of Helsinki, for patients to be eligible for the study. The consent procedure will be performed as per the approved procedure for the WOMAN trial.

Briefly, advanced information about the trial will be given to pregnant women, which will make the recruitment and consent procedure easier. The consent process will depend on the clinical emergency and the patient’s physical or emotional state. If the woman is fully competent, the healthcare giver will provide information and discuss with her about the study and obtain informed written consent (
Supplementary File 1 and
Supplementary File 2). If the woman’s mental or physical capacity does not allow her to give consent, the woman’s relative or representative, if available, should be informed about the trial and informed written consent will be obtained by them (
Supplementary File 1 and
Supplementary File 3). Where no relatives or representative are available, a waiver of prior written consent has been approved for the WOMAN trial. Where a waiver of prior written consent is used, the woman, relative or representative should be asked for consent for the continuation of the trial procedure.

To minimize the need for multiple information sheets and consent forms, one form, which combines the WOMAN trial and the WOMAN-ETAPlaT study, will be used.

## Data collection and monitoring

### Data collection

All study data will be gathered on the WOMAN trial entry data form (baseline information) and outcome data form (patient death, discharge from the hospital or 42 days after randomization). Additional information will be collected with ETAPlaT data collection forms (
Supplementary File 4). All study data will be sent electronically to the main database of the TCC in London, UK. ETAPlaT data collection forms will include the following:

Time when the blood sample was taken and laboratory analysis was started and completed, and any technical problems with analysis;Laboratory results of Multiplate analysis (ADPtest, TRAPtest), TGA, D-dimer, fibrinogen, F V, FVIII and vWF;Treatment given that may affect coagulation;Other data about the woman’s parity, BMI, gestational age at birth, maternal pre-existing conditions (anaemia, cardiac disease, haemoglobinopathy, chronic hypertension, renal disease, treatment or prophylaxis with antithrombotic drugs, or history of previous thromboembolism), pregnancy related conditions (preeclampsia, diabetes, infection, placental abruption), labour induction/augmentation and duration, anaesthesia (epidural, spinal or general), birth weight, additional doses of uterotonics (oxytocin/methergine).

